#### Incidental findings

Incidental findings are defined for the purposes of this study as any abnormalities or diseases identified on the CT scan other than lung cancer or lung nodules. It is expected that screening will detect incidental findings. Table 2 outlines categories of incidental findings, required action and follow-up to ensure action was undertaken.

Table 2: Categorisation of incidental findings, actions required and follow up

| **Category** | **Required action** | **Follow up** |
| --- | --- | --- |
| 1: major findings that may be life threatening and direct referral to hospital is required | Direct referral to hospital by radiologist or, if the participant is not on-site the radiologist will call the participant’s GP | Research nurse to call radiologist/GP to ensure referral done immediately |
| 2: significant findings (e.g. significantly dilated aortic aneurysm) requiring urgent referral | Urgent referral by participant’s GP | Research nurse to liaise with GP to ensure referral done within two weeks after report is issued |
| 3: findings indicative of cancer at another site (e.g. breast) or ctDNA information, after validation in a clinical grade test, requiring urgent referral; | Urgent referral by participant’s GP in liaison with oncology / respiratory specialists on project team. |  |
| 4: other non-cancer findings requiring non-urgent referral to primary or secondary care (e.g. significant fibrotic interstitial lung disease, TB, bronchiectasis) | Treatment by GP or non-urgent referral (by GP) to tertiary care | Study nurse to follow up on referrals in Éclair one month after report is issued |
| 5: non-cancer findings that may require management in primary care (e.g. COPD, ectatic aorta, coronary calcification) | Management by GP | Study co-ordinator to call GP to ensure patient has been seen |
| 6: findings that are usually not directly associated with a beneficial intervention (e.g. bronchial wall thickening) | No management required |  |

#### Biomarker-related incidental findings

Potential incidental findings identified via biomarker analysis will be reviewed by an external advisory group set up by [name]. This group is a Māori advisory group which already advises [name] on other projects and will be leveraged to also advise on this project, particularly around the interpretation of results and whether incidental findings are significant enough to be fed back to participants. Should any results from this study need to be discussed, the study PI or their delegate will also attend. Any actionable finding will be dealt with by the respiratory and oncology specialists in the research team, who will also provide support to the participants GP as needed.

### CT scan result management and follow up

#### Communication to participants and their whānau

In the GP arm, the GP or practice nurse will discuss the results of the scan with the participant and their whānau. For participants with clear or negative scans, this will involve a phone call from the nurse. With more complex results, the participants will be invited back to the practice for a discussion with the GP (at no cost to them). Should further scans or diagnostic investigations be required, the GP will refer the participant to the relevant tertiary service.

In the centralised arm, if no follow up is required, then the study nurse will contact the participant to inform them of the result. For participants with positive scans, the participant’s GP will contact the participant to arrange an appointment to discuss their results, and to arrange follow up (interval) CT scans and referrals for diagnostic investigations, with support from the study respiratory physician.

In both arms, participants will again be taken through their options, using a shared decision making process. Participants will always have a choice in the types of investigations they undertake and / or treatment they receive and are able to choose to decline if they wish.

#### Referrals

In both arms the participants’ scan results will be sent to the GP practice, and the study co-ordinator. Positive scans will also be sent to the study respiratory physician. In all reports, the screening radiologist will clearly categorise the scan, including recommendations for follow up and who is responsible for each action (Table 1). The report will also identify who is responsible for arranging any required follow up.

In both arms, positive scan results will be communicated to participants via their GP and, where required, the study respiratory physician. The study co-ordinator will follow up with the GP and with the study respiratory physician two weeks after receiving the report to ensure the patient has been informed of the scan result and any required follow up arrangements instituted.

Should further investigation be required, then the study respiratory physician will contact the participant to arrange appropriate follow up (Figure 3). The study co-ordinator will follow up with the study respiratory physician two weeks after receiving the report to ensure the patient has been informed of the scan result and any required follow up arrangements instituted.

Participants requiring follow up CT scans and diagnostic investigations will be referred by the respiratory physician to the relevant DHB services for ongoing care. People who are diagnosed with lung cancer will be referred to the Multi-Disciplinary Team of their DHB of domicile.

Timelines for all above procedures and discussions / referrals will be recorded and monitored by the study team to ensure timely follow up of participants and to feed into the study analysis.

### Results of COPD assessment

#### Participants

At the end of the assessment the nurse will discuss the spirometry results, CAT score and GOLD classification with the participant and their whānau. Where the results are consistent with a diagnosis of COPD the nurse will provide the participant and whānau with information about COPD and its management, including the health benefits of diagnosis and good quality management (reduced symptoms and progression of COPD) and the opportunities for increased participant and whānau self-management and autonomy over the condition. The nurse will use standardised resources developed specifically for the study. The resources will incorporate design features that support the development of participant’s/whānau COPD-related health literacy. All participants who are current smokers will be provided with brief advice and offered help to quit smoking after they have discussed the results of their COPD assessment with the nurse. The nurse will follow up with the participant/whānau 1-2 weeks after the assessment to ascertain how they are feeling about the diagnosis and discuss any questions or issues that have arisen since the assessment.

#### Participant’s GP

The GP will be sent a standardised letter including the measured FVC and measured FEV1, (with calculated % of predicted value) and the FEV/FVC ratio. The GOLD classification of severity (GOLD A (mild), B (moderate), C (severe) or D (very severe)) will be included in the letter. In addition the participant’s CAT score with an explanation of the participant’s score, and COPD-X guideline management recommendations for the participant’s GOLD classification will be included in the letter. Non-COPD related findings observed on spirometry (e.g. restrictive airflow) will also be reported on the letter to GPs.

#### Referral for specialist assessment

In addition to the provision of information to their GP, the ADHB COPD health pathway will be used to determine if participants with moderate or severe COPD (GOLD classification B, C and D) should be referred for specialist assessment at their local respiratory clinic. [name] will review results for all participants with GOLD B, C, or D classifications to confirm if referral is required.

### Results of biomarker study

The collection of blood and analysis of biomarkers is, at this stage, a feasibility study to assess how this might be built in to a future lung cancer screening programme. At this stage, we do not anticipate the analysis of the blood will be done in “real time”and we anticipate the potential for any incidental findings will be low. However, should any results be considered important, these will be reviewed by a Māori expert advisory group who will comment on whether they believe the findings to be clinically actionable. Any such results will also be reviewed by the lung cancer screening study Steering Group and Technical Advisory Group, and should there be agreement, actionable results will be shared with the patients general practitioner, who will be provided with support as to how these results will be communicated.

### Secondary research questions

As part of the study, we will also seek to determine the answers to our secondary research questions, including information on participant and provider burden, and the experience of participants at different stages of the LCS process.

Although the primary focus for this study is on testing invitation strategies, the effectiveness of LCS pathways has not yet been determined for any indigenous population including Māori. Therefore, we plan to assess our approach using an “Effectiveness-Implementation Hybrid Type II design”^47^, using both the RE-AIM^48^ framework planning questions and a locally developed kaupapa Māori implementation framework *He Pikinga Waiora*^49^. This framework has indigenous self-determination at its core and includes: cultural centredness, community engagement, systems thinking, and integrated knowledge translation (Table 3).

Key qualitative questions we wish to address include answers to the following questions:

- What is the participant and provider experience of LCS and COPD assessment
- What is the experience and acceptability of the shared decision making and results management processes as outlined in the protocol?
- What is the participant burden using the tools outlined in the study methods?
- What is the provider burden using the processes outlined in the GP clinic based arm of the study?
- What are the barriers and facilitators for participating in COPD assessment?
- How do the COPD assessment and its findings impact the participant and whānau?
- What are participant views about whether COPD should be included in future LCS?
- What are participant views around blood biomarker analysis?
- What percentage of participants offered biomarker analysis accept the offer?
- What is the feasibility / patient experience of taking blood in a single visit alongside a CT scan and spirometry?

These will be addressed using the questionnaires included in Appendices 8-17, alongside focus groups, interviews and feedback from primary care providers. Our approach will record feedback and experiences of participants (and non-participants) and providers, allowing us to incorporate this into future refinement of the process.

Our previous focus groups and surveys have fed into the development of this study, in fact our primary research question was generated from our survey finding of equipoise between the potential invitation strategies. Determining real world effectiveness of different invitation methods is therefore a key area of focus.

After the initial 50 participants have been scanned, we will review participant and stakeholders experience to assess acceptability and appropriateness of the process and to improve feasibility. We will ensure that feedback from both primary care partners and hospital partners is incorporated to minimise workflow impacts. We have localised a Canadian readiness assessment tool^50^ to prepare for potential service impacts (radiology, pathology and respiratory outpatient clinics). This will be conducted prior to the trial commencing to ensure that the trial does not have significant negative impact on participating services. Stakeholder feedback will be recorded throughout the trial.

#### COPD assessment – qualitative review

Following the COPD assessment, a qualitative assessment of participants’ experiences will be conducted and we will also seek their views on the inclusion of COPD assessment in future LCS programmes.

All COPD assessment participants will be asked to complete a short survey, and, in addition, they will be asked if they would like to be contacted to discuss their experience (e.g. positive, negative, facilitators and or barriers) related to the COPD assessment process in more depth. Patient information will then be collated (name, age, gender, contact details, health alerts, date and location of COPD assessment) and stored on a password protected database separately from all other LCS and COPD assessment study information. The information will then be supplied in a password protected spreadsheet to [name] (Te Atiawa/Kai Tahu) – National Hauora Coalition, who will lead this part of the study.

Participants will be contacted and invited to share their experience through participation in interviews. The study anticipates 50 whānau will be interviewed using the guide included in Appendix 17. The participants will be stratified on: gender, age and location (residential and locality of assessment) to ensure a representative sample of the population is interviewed.

This qualitative component is underpinned by Kaupapa Māori research principles, which consider a Māori world view and Māori ways of knowing, being and doing. As well, it centres Māori aspirations and equitable health outcomes. The qualitative component will support research skill development of a Māori research assistant.

Participants who consent to being contacted to discuss their experience of the COPD assessment process will be eligible for this component of the study. If the participant wishes, whānau members will be welcome to participate in the interview. We envisage 10% of those screened and assessed (n=50) COPD participants will be contacted and interviewed within a 6-week (to cater for recall and richness of experience) period of undergoing their COPD assessment. Semi-structured in-depth interviews will be undertaken using a method of the participant’s choosing (face-to-face, phone, zoom or similar digital conferencing) as well as preference for support, time and location (home, place of work, local café). Interviews will be recorded with participant consent. An interview schedule will be used to guide the discussion. It is anticipated that interviews will take approximately 30-60 minutes; however, this will be guided by the participant at the time.

All care will be taken to ensure health and safety of participants and interviewers (e.g. phone interviews, mask wearing and distance if face to face occurs, sanitising). A koha of $25 will be offered post interview in recognition of participant time and knowledge. The interviews will be transcribed verbatim and deidentified. The transcriber will sign a confidentiality agreement and interview transcripts will be reviewed by the interviewer to ensure correct information was captured and stored in an electronic file at National Hauora Coalition that will be password protected. These will only be accessible to the research team.

Once transcribed, the research team will independently code the de-identified transcripts. From this the research team will meet and using the give-way rule, coding the transcripts by consensus to create a coding framework. The give way rule pre-empts and acknowledges that there are different interpretations of research depending on worldview; where there are differing interpretations, the decision will be given to a senior researcher who holds Māori experience – so that the final interpretation of an idea or scenario is given to a Māori team member (Naepi, 2015). This coding framework will be reviewed by te Rōpū Rangahau at NHC; which is comprised of NHC kaimahi, from a variety of backgrounds; to ensure the framework is appropriate.

The framework will then be used in collaborative analysis; where research staff discuss each transcript together to jointly agree on an interpretation against the coding framework. The raw findings will then be presented to te Rōpū Rangahau, where feedback will contribute to a refined coding for the transcript. This process will be used for each transcript to ensure robust interpretation. Once each transcript is coded; key themes will be discussed, recording and provided back to the community/participants for review.

This will provide a detailed thematic analysis of participant’s experience of their COPD assessment. Common themes and differences between participant sub-groups (age, sex, GOLD classification and place where CT scan undertaken) will also be described. nVIVO software will be used to will be code, categorise and manage the data from the interview transcripts.

Note: an unpublished NZ study that undertook qualitative interviews with COPD patients found that many, especially those with mild and moderate disease, were not aware that their symptoms were abnormal because of the slow onset and gradual decline of their respiratory function and consequently did not raise these as issues with their health professionals.

Analysis of data collected during the recruitment of participants and study data collection will be used to answer the following quantitative questions around data:

- Provide an early description of LCS outcomes (including number of cancers detected, stage of cancers etc.). In addition to providing a description, these data will be used to update the cost effectiveness model developed previously by our research group^45^.
- What is the accuracy of recording of smoking history in general practice?
- What % of Māori ‘not never smokers’ aged 55-74 in a general practice are potentially eligible for lung cancer screening
- What % of potentially eligible people agree to undergo risk assessment
- What % of those undergoing risk assessment are eligible for lung cancer screening
- What % of those eligible for lung cancer screening decide to proceed with screening
- What % of those who decide to proceed with screening attend their appointment for screening.
- What % of patients with ctDNA identified had a nodule identified on CT scan?
- What is the concordance between patient-reported smoking history and blood plasma estimation of smoking exposure?

Table 3: Implementation science dimensions and outcomes

| **Dimension** | **Element/level** | **Outcomes** |
| --- | --- | --- |
| Reach | Describe target audience & proportion reached | Participation proportion for Primary outcome 1 - of proportion of eligible population completed risk assessment  Number excluded and reasons  Record contact type responded to (letter, phone, text, social) |
|  | Comparison of sample to the target population | Representativeness of risk assessment participants and non-participants (by age, gender and smoking history)  Representativeness of CT scan participants compared to those eligible for CT scan but did not consent to one/attend for scan |
| Effectiveness | CT scan uptake | Participation proportion for Primary outcome 2 - proportion of people eligible and who complete CT scan, by invitation arm  Number excluded and reasons |
|  | Quality of life  Participant experience | We will include a dimension based (Hua Oranga) (see Appendix 13)  Participant interview including anxiety and appropriateness of SDM, level of information, study materials and value of screen to participant and whānau |
| Adoption | Staff | Number and description of delivery agents (e.g. practice nurse, GP) per practice. Number and description of non-participants.  Number of staff attending standardised training session including an implementation manual and guide to the advanced form data entry system embedded in their Practice Management System (PMS). Pre and post training survey of knowledge and confidence, particularly in providing SDM. Survey include ability to feedback to improve future training (see Appendix 17)  For all above measures, timelines will also be monitored. |
|  | Setting | Proportion of primary care practices offered participation who choose to participate  Characteristics of participating and non-participating practices |
|  | System impacts | Audit against readiness assessment assumptions |
| Implementation | Setting | Number of claims & cost for completed screen events per practice  Triangulated with completion of the advanced form (checklist tool) for screen event – this tool will capture the key events for fidelity, time to complete the screen, text field for adaptations/issues/fixes to consider  Fidelity triangulated with research nurse observations of risk assessment completion  Ongoing partnership with providers and key stakeholders with iterative feedback including on barriers and adaptations made  Updating our cost effectiveness model with trial data |
| Maintenance | Individuals | Incorporation of Consumer Advisory Group feedback ongoing  Participant and whānau questionnaires including asking whether they would recommend participation to friends & whānau, what more could be done to reach eligible people, recommendations (covers a range of RE-AIM dimensions)  Although not within this protocol, we are planning for a (funding dependent) 2^nd^ and 3rd screening round. We propose to contact round 1 participants at 12 months post intervention to determine willingness to be re-screened |
|  | Setting | Debrief post trial with key stakeholders including consumer advisory group, primary care and hospital stakeholders.  Provider focus groups and/or interviews (covers a range of RE-AIM dimensions) |

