### Full trial

#### Primary outcome:

The full trial including a further 500 scans of eligible participants will address the primary research question of whether an invitation to lung screening conducted in primary care results in higher levels of participation by Māori than a central hub-based invitation method.

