## Statistical Consideration and Data Analysis

### Sample size and statistical analysis

The sample size for the overall randomised trial is calculated based on the power required to test the hypothesised difference in the number of participants completing lung cancer screening following an invitation to the study. Our sample size will provide more than sufficient power to test the hypothesised difference in completion of risk assessment. Sample size was calculated using the formula cited in Hade et al^51^. Table 4 outlines the assumptions made in the sample size calculation.

Table 4: Assumptions used in power calculation (MAIN STUDY)

| **Parameter** | **Assumed value** | **Justification** |
| --- | --- | --- |
| Proportion of Māori aged 55-74 who meet eligibility criteria to be invited for screening | 24% | Smoking history data collected in our pilot of AAA screening (28%), reduced by 4% to allow for those excluded on other grounds (terminal illness etc.). |
| Intraclass correlation coefficient | 0.03 | Approximately the median value of those cited in Hade et al. |
| Average number of eligible patients per practice | 24 | From practice population registers. Practices with <10 expected eligible patients will be excluded. |
| Proportion of Māori in eligible age range recorded as not “never smokers” | 70% | Data from one of the Auckland PHOs. |
| Proportion of not never-smokers eligible who complete risk assessment in the primary care group | 80% | It is difficult to estimate this parameter as there is no similar experience to base it on. However it would seem reasonable that it is possible to obtain smoking history on 70% of the eligible practice population in the control group, and that this could be 10% higher in the intervention group where primary care may have a significant advantage. |
| Proportion of not never-smokers eligible who complete risk assessment in central hub group | 70% |  |
| Screening uptake in the central hub group | 40% | Based on uptake rates routinely achieved for Māori in other screening programmes including bowel screening. |
| Screening uptake rate in primary care group | 50% | A goal of 10% higher uptake rate than the control group is both achievable and clinically meaningful |
| Variance reduction from regression adjustment of individual-level outcomes. | 10% | Consistent with variance reduction assumptions used by Hade et al. |

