## Outcomes and Significance

### Primary outcome

To determine the effectiveness of two invitation strategies: primary care vs central hub.

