### Secondary outcomes

Secondary outcomes include:

**Eligibility for risk assessment:** Proportion identified as potentially eligible by PHO list who were eligible for risk assessment.

**Completion of Risk assessment:** Proportion of participants who were eligible for risk assessment that completed the risk assessment process. Also an assessment of the differences between the primary care and central hub groups.

**CT scan eligibility:** Proportion of those who underwent risk assessment that met risk threshold for a CT scan by PLCO_M2012_ and criteria-based eligibility.

**Effectiveness of engagement in shared decision making:** proportion of eligible participants that decide to proceed with screening after participating in a shared decision making process to discuss the risks and benefits.

**LCS screening uptake among those eligible:** proportion of those that agree to lung cancer screening who attended and underwent the scan.

- Participant and provider experience of LCS
- Experience and acceptability of the shared decision making and results management processes
- Participant burden using the tools outlined in the study methods
- Provider burden using the processes outlined in the GP clinic based arm of the study
  - The burden on staff and participants will be measured through follow-up interviews and/or focus groups conducted by a member of the research team following the implementation of the pilot.
- Provision of a description of LCS outcomes. This will include The positivity rate of CT scans; the proportion of scans with incidental findings; proportions who proceed to nodule management (interval scans); diagnostic investigations; incidental finding management; the number, stage and types of cancers; response to brief advice to quit; and smoking cessation medications provided and referrals made.
- Assessment of the accuracy of recording of smoking history in general practice

**Prevalence of COPD among those eligible for LCS:** proportion of those eligible who have a spirometry-based COPD diagnosis.

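### The protocol contradicts itself on its primary outcome: Table 3 names two, the outcomes list makes one of them secondary, and no section names the powered quantity as the sole primary

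*Protocol*

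**What the plan says.** Five places in the protocol bear on the primary outcome.

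- **Aims and objectives, Full trial.** The primary question is whether a primary care invitation "results in higher levels of participation by Māori than a central hub-based invitation method". Participation is not tied to a step of the pathway.
- **Table 3, Reach row.** "Participation proportion for Primary outcome 1 - of proportion of eligible population completed risk assessment".
- **Table 3, Effectiveness row.** "Participation proportion for Primary outcome 2 - proportion of people eligible and who complete CT scan, by invitation arm".
- **Outcomes and Significance.** The entry under Primary outcome is "To determine the effectiveness of two invitation strategies: primary care vs central hub", which is an aim with no numerator or denominator. Under Secondary outcomes, risk-assessment completion appears as "Proportion of participants who were eligible for risk assessment that completed the risk assessment process", followed by "Also an assessment of the differences between the primary care and central hub groups". The item whose title refers to screening uptake among eligible people is defined as "proportion of those that agree to lung cancer screening who attended and underwent the scan".
- **Sample size and statistical analysis, with Table 4.** The trial is sized on the "hypothesised difference in the number of participants completing lung cancer screening following an invitation to the study". The text adds that power is more than sufficient for the difference in risk-assessment completion. Table 4 gives one type I error rate (5%) and one power figure (80%), the latter for a 10% increase in screening uptake.

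**The concern.** Risk-assessment completion is primary in one section and secondary in another. CT completion is primary in Table 3. In the outcomes list, its nearest counterpart is a secondary item whose title and definition use different denominators. An analysis plan could follow either section and still comply with the protocol.

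Two things are at stake. The first is what the single 5% tests: one comparison, two that share it, or two at 5% each. The second is the denominator of the scan outcome. CT eligibility is known only after risk assessment, and Table 4 expects completion of that step to differ by arm (80% vs 70%). Scans per CT-eligible person and scans per invited person are therefore different questions and need not give the same answer. Leaving the choice open until data are in hand is a real weakness in a trial meant to inform a national programme.

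**Working it through.** **Inputs.** From Table 4: uptake 40% (central hub) and 50% (primary care); ICC 0.03; 24 eligible patients per practice; variance reductions of 10% (individual level) and 20% (group level); risk-assessment completion 70% and 80%; 24% of Māori aged 55-74 eligible for screening and 70% not recorded as never smokers; 5% error; 80% power. From Study setting/Location: 24 practices per arm. From the Synopsis: 4412 invited, 3309 risk-assessed, 1134 eligible for CT, 500-550 scans.

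**1. Reproduce the plan's own figure.** Practices per arm:

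g = (z₀.₉₇₅ + z₀.₈₀)² × 2p̄(1−p̄) × [(1−ICC)×0.9/m + ICC×0.8] / d²

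With p̄ = 0.45, d = 0.10 and m = 24:

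- 2p̄(1−p̄) = 0.495
- bracket = 0.97×0.9/24 + 0.03×0.8 = 0.060375
- g = (1.960 + 0.842)² × 0.495 × 0.060375 / 0.01 = 23.46, rounded up to 24
- eligible people = 2 × 23.46 × 24 = 1126, against 1134 stated

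A one-sided 5% test would need only 18.5 per arm, so the 5% is two-sided. The Synopsis funnel agrees: 4412 × 0.75 = 3309; 3309 × 24/70 = 1134; 1134 × 0.45 = 510 scans.

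Power at 24 per arm: SE = √(0.495 × 0.060375 / 24) = 0.0353; 0.10/0.0353 = 2.834; Φ(2.834 − 1.960) = 80.9% (79.2% with a t reference). The stated 80% therefore belongs to CT completed among CT-eligible people, which is the second primary outcome of Table 3.

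**2. All-invited denominator.** Scans per invited person:

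- central hub: 0.70 × 24/70 × 0.40 = 9.6%
- primary care: 0.80 × 24/70 × 0.50 = 13.7%

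With m = 4412/48 = 91.9, the bracket is 0.97×0.9/91.9 + 0.024 = 0.0335. With p̄ = 0.1166, 2p̄(1−p̄) = 0.206. SE = √(0.206 × 0.0335 / 24) = 0.01696; 0.0411/0.01696 = 2.427; power = Φ(2.427 − 1.960) = 68% (60% without the variance reductions).

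**3. Risk-assessment completion, 70% vs 80%.** With m = 91.9 and p̄ = 0.75, SE = √(0.375 × 0.0335 / 24) = 0.0229; 0.10/0.0229 = 4.37; power = 99% with Table 4's variance reductions and 98% without them.

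**4. Two primaries and one 5%.**

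- Both tested at two-sided 5%, either sufficient: 1 − 0.95² = 9.75% if independent. From the bivariate normal: 9.5%, 9.1% and 8.3% at correlations 0.3, 0.5 and 0.7.
- Split equally, 2.5% each: power for CT uptake = Φ(2.834 − 2.241) = 72.3%. Restoring 80% would take g = 28.4, that is 29 practices per arm.

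**5. Attendance among those who agreed.** The documents give no planning rate for this quantity, so no power can be attached to it.

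**The case against.** The strongest reply is that the powered outcome is not in doubt. The sample-size section sizes the trial on completed screening, Table 4 ties the 80% to uptake, and the arithmetic leads to one quantity that Table 3 already defines. A reader might infer from the conflicting labels that the 5% and the 80% belong to no outcome at all. The documents do not support that, and the sample size is not at fault.

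A reader might also infer that the trial runs an 8-10% false-positive rate, or that it would be declared positive on risk assessment alone. That needs a rule that either outcome suffices at 5% each, and the protocol states none. It treats the two unequally: only the scan outcome determines the size, and only that Table 3 row specifies comparison by arm. Error control across outcomes may be set in an analysis plan that is not shown. The figures in step 4 are therefore conditional.

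Finally, the item defined over those who agreed is one step of a descriptive pathway, and nobody proposes it as primary. The preceding step uses eligible people as its denominator, and the product of the two is uptake among the eligible. What remains there is a title that does not match its definition.

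None of this removes the contradiction between Table 3 and the outcomes list. Which variable is primary is for the protocol to fix, and here it gives conflicting answers. The text also foresees testing risk-assessment completion, so a second comparison between arms is planned.

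**Conclusion.** The concern stands as a contradiction about which outcome is primary and over which denominator. The design delivers its stated power for CT completed among CT-eligible people (80.9%). No section names that quantity as the sole primary, and the sample-size wording leaves room for an all-invited denominator with about 68% power. If the two Table 3 primaries were both kept, the cost would be either a false-claim rate of up to 9.75% (8.3% at correlation 0.7), if either sufficed at 5%, or power of about 72% for CT uptake under an equal split.

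These figures assume that Table 4's ICC and variance reductions hold for every outcome considered, that practices are of equal size, and that the normal approximation applies. The correlations are assumed. The contradiction itself rests on the text alone. It should be resolved before analysis, because it changes what the trial can claim.

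**What to change.** - Name one primary outcome, with its denominator, in the Full trial section, Table 3, the sample-size text and Outcomes and Significance: CT scan completed among those eligible for CT, compared between arms. This is the quantity to which the stated 80% belongs. If all invited people are the intended denominator, say so and restate the power as about 68%.
- In Table 3, relabel risk-assessment completion as the key secondary outcome, tested at 5% only if the primary is significant.
- In the secondary outcomes, make the definition of uptake among eligible people match its title, and rename the present definition as attendance among those who agreed.

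The cost is wording in four places. The fixed order takes no power from the primary and needs no extra practices. Splitting the 5% would also be valid, but would need about 29 practices per arm to keep 80% power for CT uptake.
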